# Effect of Low-Intensity Transcranial Focused Ultrasound Stimulation on Neuropathic Pain: Protocol for a Randomized, Single-Blind, Placebo-Controlled, 3-Arm, Parallel-Group Trial

**DOI:** 10.2196/95379

**Published:** 2026-08-14

**Keywords:** transcranial focused ultrasound stimulation, noninvasive brain stimulation, neuropathic pain, protocol, randomized controlled trial

## Abstract

**Background:**

Neuropathic pain (NP) remains difficult to manage because conventional pharmacological therapies often have limited efficacy and intolerable side effects. Noninvasive neuromodulation techniques have emerged as potential alternatives with fewer adverse effects. Meta-analyses of randomized controlled trials suggest that high-frequency repetitive transcranial magnetic stimulation over the primary motor cortex has analgesic effects; however, its efficacy is modest and restricted by the inability to stimulate deeper brain regions. Low-intensity transcranial focused ultrasound stimulation (TUS) is a novel approach that enables precise targeting of deep brain structures and modulation of neural activity. Although promising in preclinical and preliminary human studies, its long-term therapeutic efficacy for NP remains unknown.

**Objective:**

This trial aims to explore the therapeutic effects and safety of repeated TUS sessions in patients with NP.

**Methods:**

This randomized, participant-blinded, placebo-controlled, 3-arm, parallel-group clinical trial will enroll 39 participants with NP (pain duration ≥3 months; pain intensity ≥4 on the numerical rating scale). Participants will be randomly allocated to one of three groups: (1) TUS targeting the primary motor cortex, (2) TUS targeting the posterior superior insula, or (3) sham stimulation. Each participant will undergo weekly sessions for 8 weeks. The primary outcome is change in weekly average pain intensity scores recorded in a pain diary. Secondary outcomes include additional pain scales, quality of life measures, psychological assessments, quantitative sensory testing, motor cortical excitability, and adverse events.

**Results:**

The first participant was enrolled on April 30, 2025, and 20 participants had been enrolled as of February 28, 2026, with enrollment ongoing. The final analysis will be conducted after completion of follow-up and data verification.

**Conclusions:**

To our knowledge, this will be the first randomized controlled trial to examine the long-term therapeutic effects of repeated low-intensity TUS for NP. It will provide exploratory proof-of-concept data regarding its clinical efficacy and safety.

## Introduction

Neuropathic pain (NP) is defined by the International Association for the Study of Pain as “pain caused by a lesion or disease of the somatosensory nervous system” [1]. It often persists after the original injury has healed and is typically resistant to standard pharmacological treatments. Common forms include postherpetic neuralgia, painful diabetic neuropathy, phantom limb pain, spinal cord injury–related pain, and central poststroke pain. A nationwide Japanese epidemiological survey estimated the prevalence of NP at 3.2%, corresponding to approximately 3.5 million adults in Japan [2]. Despite available therapies, many patients report inadequate pain relief, and adverse effects frequently limit long-term adherence. First-line agents such as gabapentinoids, tricyclic antidepressants, and serotonin-norepinephrine reuptake inhibitors are recommended, but their effectiveness remains limited, with numbers needed to treat ranging from 4.6 to 8.9 [3]. Repetitive transcranial magnetic stimulation (rTMS), a noninvasive neuromodulation technique that targets the primary motor cortex (M1), has been investigated as an alternative. Systematic reviews and meta-analyses suggest that rTMS provides analgesic benefits [3-5], although the efficacy remains modest, with a number needed to treat of 4.2. In our previous clinical trials, rTMS showed limited benefit for pain overall, and subgroup analyses revealed particularly reduced effects for lower-limb pain, likely because rTMS cannot adequately stimulate deeper cortical regions such as the M1 foot area [6-8]. Because the M1 foot region and many other pain-related structures are located deep within the brain, further development of noninvasive therapeutic strategies capable of modulating these targets is needed.

In recent years, focused ultrasound has been increasingly developed and applied for a variety of purposes. This technology delivers ultrasound at frequencies above 20 kHz through the skull and can be directed to a localized brain region, allowing for intervention in deep brain structures. Magnetic resonance–guided focused ultrasound for thalamic thermal ablation is already used in clinical practice for the treatment of tremors, whereas ongoing studies are exploring its role in microbubble-mediated opening of the blood-brain barrier. More recently, low-intensity transcranial focused ultrasound stimulation (TUS), which operates at intensities below 100 W/cm^2^, has emerged as a noninvasive technique to modulate neural activity from outside the skull. Over the past two decades, animal studies have shown that TUS can alter motor-evoked potentials (MEPs) and regional cerebral blood flow [9]. Since its first application in humans in 2013, TUS has been reported to shorten reaction times in motor tasks, modulate somatosensory and visual-evoked potentials, and influence perception. The proposed mechanism involves ultrasonic acoustic pressure acting on ion channels through mechanoreceptors, thereby modulating neuronal activity [10].

TUS is a novel technique capable of exerting localized effects on deep brain structures without surgery. In contrast, rTMS can stimulate only superficial cortical regions when applied focally, and attempts to target deeper areas inevitably result in diffuse activation. To date, no rTMS device has been developed that allows for precise stimulation of deep brain structures. Potential therapeutic targets for NP include the M1 foot area, insula, cingulate gyrus, and thalamic nuclei. Although rTMS has been unable to adequately stimulate these regions, TUS may offer this capability. Thus far, only 2 studies of TUS in the context of pain have been conducted in healthy participants [11,12], and 1 single-arm study has been reported in patients with NP [13]. We previously performed a sham-controlled randomized crossover feasibility study of TUS in patients with NP (jRCTs052230116). However, to the best of our knowledge, no randomized controlled trial has yet evaluated the clinical efficacy of TUS for NP. For clinical translation, the so-called offline effects—sustained aftereffects that persist beyond the stimulation period—are considered essential. As with rTMS, repeated sessions, rather than a single session, are likely required to achieve meaningful therapeutic benefits.

Given the exploratory nature of this preliminary study, we selected 2 stimulation sites—M1 and the posterior superior insular cortex (PSI)—to assess their potential therapeutic effects. M1 was chosen based on extensive evidence from prior clinical studies using rTMS [3-5], whereas the PSI was selected because it is a major projection site of the spinothalamic tract and plays a key role in pain perception [14]. Furthermore, previous reports have shown that deep brain stimulation of the PSI can alleviate pain [15]. The aim of this study is to explore the efficacy and safety of weekly TUS administered over 8 weeks in patients with NP to provide proof-of-concept data for this therapeutic approach.

## Methods

### Trial Design

This study is a randomized, single-blind (participant-blinded), placebo-controlled, parallel-group clinical trial conducted at the University of Osaka Hospital in Japan. Because pain is highly susceptible to placebo effects, a sham stimulation group was included as the control group to evaluate the superiority of active stimulation. A parallel-group design was selected instead of a crossover design owing to concerns about potential carryover effects and the risk of unblinding. To further explore potential differences in efficacy, 2 active stimulation sites were designated. The study flowchart is shown in Figure 1.

**Figure 1. F1:**
[figure not shown]
Flowchart of the study design. M1: primary motor cortex; PSI: posterior superior insular cortex; TUS: transcranial focused ultrasound stimulation.

This study is an investigator-initiated clinical trial. Trial monitoring and auditing will be conducted by an independent academic research organization (Department of Medical Innovation, University of Osaka Hospital). Monitors will perform oversight in accordance with the monitoring plan to ensure data reliability and participant protection, verifying compliance with applicable laws, regulations, and the trial protocol, and will prepare monitoring reports. Data will be captured using an electronic data capture system (REDCap; Research Electronic Data Capture; Vanderbilt University), which minimizes input error, duplication, and missing data while ensuring security and transparency. This paper is based on protocol version 1.3 dated March 25, 2025.

### Participants

We will enroll patients aged 18 years or older with NP who meet the following inclusion criteria: (1) NP persisting for more than 3 months, (2) pain intensity score of 4 or more on the numerical rating scale (NRS) at screening, and (3) written informed consent to participate in this study. The definition of NP follows the International Association for the Study of Pain terminology [1], adopting a classification of probable or definite NP according to the NP grading system [16]. Exclusion criteria are as follows: (1) dementia with a Mini-Mental State Examination (MMSE) score of 23 or lower; (2) severe aphasia or cognitive dysfunction; (3) serious psychiatric disorder; (4) history of epileptic seizures; (5) use of an implantable stimulator, such as a cardiac pacemaker, except for implantable spinal cord stimulators; (6) metallic implants in the head, except for titanium products; (7) use of an implantable drug delivery system or implantable ventricular assist device; (8) pregnancy; (9) inability to complete the assessment questionnaires; (10) participation in any other clinical trial within 3 months prior to providing consent; and (11) any other condition deemed inappropriate for inclusion by the investigators. Participants will be recruited from outpatients of the Department of Neurosurgery at University of Osaka Hospital.

Participants will be withdrawn from the study if any of the following criteria are met after enrollment: (1) the investigator determines that continuing the study poses an unacceptable risk owing to the occurrence of an adverse event; (2) the participant withdraws consent or requests to discontinue participation; (3) it is discovered that the participant does not meet the eligibility criteria; (4) the participant is unable to complete the required assessments or visits as a result of personal circumstances, such as relocation; or (5) the investigator determines, for any other reason, that discontinuation of the intervention is appropriate.

### Randomization and Blinding

Participants will be randomly allocated in a 1:1:1 ratio to one of three groups: (1) active stimulation targeting M1, (2) active stimulation targeting PSI, or (3) sham stimulation. Because the primary outcomes rely on participant-reported subjective assessments, this study will adopt a single-blind design in which participants remain blinded to group allocation throughout the trial. Blinding of the investigators delivering the intervention is not feasible with the current device. As this is a preliminary study in which most outcomes are patient-reported, investigators are not blinded. To minimize expectation effects, all groups will undergo identical procedures, including treatment duration, interaction with study personnel, and auditory masking using white noise. The success of participant blinding will be evaluated at the end of the intervention period using a blinding assessment questionnaire.

Randomization will be conducted using a stratified permuted block method, with the underlying cause of NP (central or peripheral origin) as the stratification factor. The allocation table and procedure will be generated by an independent technician who is not involved in patient enrollment or outcome assessment. Assignment will be managed through the REDCap randomization module, which enhances secure handling of allocation information using password protection.

### Trial Schedule

All patients who provide consent are assessed for eligibility by neurosurgeons specializing in pain management. Eligible participants will be randomly allocated to 1 of the 3 groups and undergo baseline evaluations, including demographic and clinical characteristics. The intervention is administered once a week for 8 weeks (Figure 2). This schedule was determined based on previous rTMS studies, which showed that intermittent stimulation—such as weekly sessions—provides significant pain relief for between 4 and 8 weeks or sessions, after which the effect tends to plateau [17-20]. Participants will be asked to record a pain diary from 1 week prior to the intervention until 1 week after completion at week 8. The NRS for pain and paresthesia (*shibire* in Japanese), along with the Short-Form McGill Pain Questionnaire version 2 (SF-MPQ-2) [21], will be assessed at baseline, immediately after each intervention, and at follow-up visits. Additional measures—including the Brief Pain Inventory (BPI) [22], EQ-5D-5L [23], Hospital Anxiety and Depression Scale (HADS) [24], Pain Catastrophizing Scale (PCS) [25,26], Pain Self-Efficacy Questionnaire (PSEQ) [27], MMSE, quantitative sensory testing (QST), motor cortical excitability, and the *shibire* questionnaire (validated by our group; [name], unpublished data, October 2024) [28]—will be assessed at baseline and immediately after the final intervention at week 8. At the end of the study, Patient Global Impression of Change (PGIC) and blinding assessments will be collected. Adverse events will be monitored continuously from the start of the intervention until follow-up visits at weeks 12 and 16 or until study discontinuation. Potential adverse events associated with TUS will be explained to participants during the informed consent process. In addition, at each treatment session, participants will be asked whether they have experienced any new symptoms or deterioration. The detailed schedule is shown in Table 1.

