**Figure 2. F2:**

Trial schedule. TUS: transcranial focused ultrasound stimulation; W: week.

**Table 1. T1:** Schedule of enrollment, intervention, and assessment.

	Baseline assessment—week 0	Preintervention period	Intervention period								Follow-up period	
			Week 1	Week 2	Week 3	Week 4	Week 5	Week 6	Week 7	Week 8^a^	Week 12	Week 16
Eligibility screen	✓											
Demographic background	✓											
Intervention			✓	✓	✓	✓	✓	✓	✓	✓		
Pain diary^b^		✓	✓	✓	✓	✓	✓	✓	✓	✓		
Pain NRS^c^ and SF-MPQ-2^d^^,^^e^	✓		✓	✓	✓	✓	✓	✓	✓	✓	✓	✓
BPI^f^, EQ-5D-5L, HADS^g^, PCS^h^, and PSEQ^i^	✓									✓		
MMSE^j^	✓									✓		
Motor cortical excitability	✓									✓		
QST^k^^,^^l^	✓									✓		
*Shibire* questionnaire^m^	✓									✓		
*Shibire* NRS^e^^,^^m^	✓		✓	✓	✓	✓	✓	✓	✓	✓	✓	✓
PGIC^n^										✓		
Blinding										✓		
Adverse events			✓	✓	✓	✓	✓	✓	✓	✓	✓	✓
Malfunction of the device			✓	✓	✓	✓	✓	✓	✓	✓		

a If the intervention is discontinued, evaluations are performed at week 8.

b Pain diary is recorded from 1 week before the intervention until 1 week after its completion (week 8).

c NRS: numerical rating scale.

d SF-MPQ-2: Short-Form McGill Pain Questionnaire version 2.

e These measures are assessed immediately after each intervention.

f BPI: Brief Pain Inventory.

g HADS: Hospital Anxiety and Depression Scale.

h PCS: Pain Catastrophizing Scale.

i PSEQ: Pain Self-Efficacy Questionnaire.

j MMSE: Mini-Mental State Examination.

k QST: quantitative sensory testing.

l Assessed if the maximum pain site is located in the upper or lower extremities.

m Assessed if *shibire* is present. “*Shibire*” is a common Japanese term describing abnormal sensations, such as paresthesia, dysesthesia, or numbness, and may also refer to motor difficulty.

n PGIC: Patient Global Impression of Change.

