### Outcomes

#### Overview

The primary outcome is the change in weekly average pain intensity scores recorded in a pain diary using an 11-point NRS ranging from 0 (no pain) to 10 (worst imaginable pain). Participants will evaluate their average pain over the previous 24 hours daily at home. Weekly averages will be calculated, and changes from the baseline week to each postintervention week up to week 8 will be assessed. The primary end point is the change in weekly average pain scores from baseline to week 8. To assess clinically meaningful improvements, responder analyses will identify the proportion of participants achieving reductions of 2 points or more and 4 points or more [35] in weekly average pain scores at week 8 compared with baseline.

Secondary outcomes comprise patient-reported and physiological measures, enabling a multidimensional evaluation of pain, functional impact, psychological status, neurophysiological response, and patient perception over time. These include both longitudinal changes from baseline and postintervention assessments across the following domains.

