Demographic characteristics and outcomes will be summarized descriptively, with longitudinal outcomes presented as line graphs over time. The primary analysis will use a linear mixed-effects model for repeated measures (MMRM) to evaluate changes in weekly average pain scores from the pain diary. The model will include change from baseline in weekly average pain scores as the response variable, with treatment group, time point, and their interaction as fixed effects and individual participants as a random effect. Baseline pain scores will be included as covariates. The primary treatment effects will be estimated using model-based contrasts comparing M1 stimulation with sham stimulation and PSI stimulation with sham stimulation at week 8. Multiplicity arising from these 2 primary comparisons will be controlled using the Dunnett adjustment. To identify time points showing significant changes from baseline, the Dunnett multiple comparison procedure will be used, with the baseline week serving as the control. The number and proportion of responders will be summarized by treatment group, and between-group comparisons will be performed using logistic regression models adjusted for baseline pain scores. Missing week 8 pain diary data will be imputed using the last observation carried forward method for responder analyses only. Secondary outcomes measured repeatedly, such as pain NRS and SF-MPQ-2, will also be analyzed using MMRM in the same way as the primary outcomes. Outcomes assessed only at baseline and week 8—including BPI, EQ-5D-5L, HADS, PCS, PSEQ, MMSE, QST, and MEP—will be evaluated using analysis of covariance, with change from baseline as the response variable, treatment group as a fixed effect, and baseline value as a covariate. Paresthesia-related outcomes will be analyzed using MMRM, analysis of covariance, or logistic regression depending on data type and timing. PGIC responses at week 8 will be summarized by treatment group and compared using the Fisher exact test. All analyses will be 2 sided, with *P* values below .05 considered statistically significant.

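### As worded, allocation precedes the baseline assessments and the diary week while investigators are unblinded, leaving staff-run baselines and pre-treatment losses open to knowledge of the arm

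*Protocol article*

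**What the plan says.** All references are to the protocol article.

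- **Order.** Trial Schedule: "Eligible participants will be randomly allocated to 1 of the 3 groups and undergo baseline evaluations, including demographic and clinical characteristics". The diary is tied to treatment, not to allocation: "Participants will be asked to record a pain diary from 1 week prior to the intervention until 1 week after completion at week 8". Table 1 puts the eligibility screen and the baseline assessments in one week-0 column and first ticks the diary in the later preintervention column. It has no row for randomisation.
- **Blinding.** Randomization and Blinding: "As this is a preliminary study in which most outcomes are patient-reported, investigators are not blinded". Of participants it says that "participants remain blinded to group allocation throughout the trial".
- **Who scores the primary measure.** Outcomes, Overview: "Participants will evaluate their average pain over the previous 24 hours daily at home".
- **Use of baseline.** Statistical Analysis, for the primary mixed model: "Baseline pain scores will be included as covariates". The responder logistic models adjust for baseline pain, and the analyses of covariance for outcomes measured only at baseline and week 8 adjust for the baseline value.
- **Analysis set.** The full analysis set needs at least one session received and at least one outcome measured afterwards, and is described as intention-to-treat.
- **Eligibility.** Participants requires pain NRS of 4 or more at screening. It excludes an MMSE of 23 or lower and people unable to complete the questionnaires.

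**The concern.** A baseline used for adjustment should be one that allocation cannot have touched. If allocation comes first and the staff taking the baseline know the arm, that safeguard is missing for measurements that staff run. Such a measurement could then be influenced at baseline as well as at week 8.

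A second route needs no altered reading. Allocation at week 0 opens an interval, containing at least the diary week, in which a participant is randomised but untreated. The withdrawal criteria include investigator judgement for any other reason, and an investigator who knows the arm can exercise it in that interval. Whoever leaves then disappears from the main analysis.

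Third, if baseline measures that also decide eligibility are read after allocation, ineligibility can come to light in someone already randomised. That leads to withdrawal, or to exclusion from the per-protocol set.

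**Working it through.** **1. Sequence.** Trial Schedule names eligibility, then allocation, then baseline evaluations. Table 1 puts the diary week after week 0. Suppose the conjunction in the sentence is not sequential and allocation happens within week 0: the diary week still follows allocation. Only allocation after the diary week avoids this, and no sentence in the article says so.

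**2. Eligibility against that sequence.** Only eligible participants are allocated. The only pre-treatment MMSE and pain NRS in Table 1 are at week 0, beside the eligibility screen. These must be known before allocation, yet Trial Schedule lists them among the baseline measures. A strict order of allocation first and all baselines second therefore cannot be right, and the sections need reconciling.

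**3. Which baselines are exposed.**
- Participant-scored: diary (primary), pain NRS, SF-MPQ-2, BPI, EQ-5D-5L, HADS, PCS, PSEQ. The scorer is blinded, so influence could come only indirectly, through staff.
- Staff-run: quantitative sensory testing, motor cortical excitability, and MMSE if taken after allocation. The article describes no blinded assessor. All are secondary.
- No baseline score: PGIC, the blinding questionnaire, adverse events.

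**4. Size of one pre-treatment loss.** The planned size reproduces. Means 34.8, 34.8 and 17.4 with SD 15.2 give f = 0.540; one-way ANOVA power is 79.7% at N = 36 and 80.9% at N = 37; 37/0.95 = 38.9, so 39, or 39/3 = 13 per arm. One loss is 1/13 = 7.7% of an arm. The whole dropout allowance is 39 − 37 = 2 participants. Moving allocation changes none of these figures.

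**5. What a shifted baseline would do (illustration only).** Let knowledge of the arm shift the recorded baseline by δ in one arm, and let β be the slope of the week-8 value on baseline. The adjusted contrast is then biased by −β × δ. Once baseline is a covariate, also subtracting it adds nothing to this bias. The assumed inputs, none from the article, are: SD 1.5 on the 0–10 scale, baseline-to-week-8 correlation 0.5 or 0.7 (equal to β here), two arms of 13, no true effect, and an unadjusted two-sided 5% test. Simulation with 6,000 runs per setting gave:

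| δ | bias (correlation 0.5 / 0.7) | type I error (0.5 / 0.7) |
|---|---|---|
| 0 | −0.003 / 0.005 | 5.4% / 4.9% |
| 0.5 | −0.247 / −0.350 | 6.9% / 11.9% |
| 1.0 | −0.493 / −0.692 | 14.1% / 31.2% |

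The formula gives the same: 0.5 × 0.5 = 0.25 and 0.7 × 0.5 = 0.35. The δ = 0 row shows that timing alone does no harm.

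**6. Who can still benefit.** Results reports 20 enrolled by February 28, 2026, so at most 39 − 20 = 19 remain.

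**The case against.** The strongest reply is that the order is inferred from one sentence. Its conjunction does not strictly fix a sequence, the article condenses a fuller protocol, and the flowchart in Figure 1 is not shown. That stands to this extent: actual practice may differ. The remedy is then to correct the sentence, because nothing in the article places allocation later.

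A reader might infer that every change score, including the primary one, rests on an openly measured baseline. The article does not support that. The diary is scored at home by blinded participants, the questionnaires are self-reported, and identical interaction with study personnel is planned across groups. Nor is a pre-treatment baseline biased merely because it follows allocation.

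It can also be said that the article does not state who learns the arm, or when, and that REDCap allocation is password protected. That is fair: exposure of the staff-run baselines is a possibility the wording leaves open, not a documented event. The limitations paragraph already concedes residual bias for secondary outcomes that involve investigators. That concession does not address baselines taken after allocation.

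Lastly, the full analysis set drops untreated participants whatever the order, no such loss is projected, and blinded participants who leave would not be reacting to their arm. All true. The order still determines how long that gap lasts, and withdrawal by an unblinded investigator remains possible within it.

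**Conclusion.** The point holds in limited form. As worded, the plan lets staff-run baselines be taken by people who know the arm, opens a pre-treatment interval whose losses leave the main analysis at 7.7% of an arm each, and sits badly with its own eligibility criteria. The exposed measures are secondary. For the primary diary any effect could only be indirect, and the article gives no evidence of one.

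The bias figures are illustrative and should not be quoted as an estimate for this trial. They need a shift that differs between arms, and its size is assumed. Setting them against the planned difference of 34.8 − 17.4 = 17.4 would further need a 0–100 scale, which the Sample Size Estimation section does not state.

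The conclusion rests on reading Trial Schedule and Table 1 as they stand. This is an inexpensive improvement worth making, not a defect that undermines the primary comparison.

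**What to change.** - For all remaining participants, trigger the REDCap allocation only after the week-0 assessments and the baseline diary week are complete and locked, on or just before the day of session 1.
- Correct the Trial Schedule sentence and add the randomisation step to Table 1, so that eligibility, baseline, diary week, allocation and session 1 appear in that order.
- Report how many of those already enrolled were allocated before their baseline measurements.
- If allocation already follows baseline in practice, correct the sentence and the table only.

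The cost is a short amendment and preparing stimulation targets before the arm is known. No visit is added and the sample size is unchanged. The benefit is that staff-run baselines are taken before anyone can know the arm, eligibility is settled before allocation, and almost no time remains in which a randomised participant can be lost untreated.
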